## Abstract

**Background:**

The PEACH study is based on an innovative 'telephone coaching' program that has been used effectively in a post cardiac event trial. This intervention will be tested in a General Practice setting in a pragmatic trial using existing Practice Nurses (PN) as coaches for people with type 2 diabetes (T2D). Actual clinical care often fails to achieve standards, that are based on evidence that self-management interventions (educational and psychological) and intensive pharmacotherapy improve diabetes control. Telephone coaching in our study focuses on both. This paper describes our study protocol, which aims to test whether goal focused telephone coaching in T2D can improve diabetes control and reduce the treatment gap between guideline based standards and actual clinical practice.

**Methods/design:**

In a cluster randomised controlled trial, general practices employing Practice Nurses (PNs) are randomly allocated to an intervention or control group. We aim to recruit 546 patients with poorly controlled T2D (HbA1c >7.5%) from 42 General Practices that employ PNs in Melbourne, Australia. PNs from General Practices allocated to the intervention group will be trained in diabetes telephone coaching focusing on biochemical targets addressing both patient self-management and engaging patients to work with their General Practitioners (GPs) to intensify pharmacological treatment according to the study clinical protocol. Patients of intervention group practices will receive 8 telephone coaching sessions and one face-to-face coaching session from existing PNs over 18 months plus usual care and outcomes will be compared to the control group, who will only receive only usual care from their GPs. The primary outcome is HbA1c levels and secondary outcomes include cardiovascular disease risk factors, behavioral risk factors and process of care measures.

**Discussion:**

Understanding how to achieve comprehensive treatment of T2D in a General Practice setting is the focus of the PEACH study. This study explores the potential role for PNs to help reduce the treatment and outcomes gap in people with T2D by using telephone coaching. The intervention, if found to be effective, has potential to be sustained and embedded within real world General Practice.

## Background

### The treatment gap and health policy in diabetes

Diabetes has reached epidemic proportions in most countries [1] including Australia [2]. The incidence of diabetes is expected to double worldwide in the next twenty years. The economic costs of diabetes are huge and are doubled by the onset of complications resulting from poor disease control. Diabetes is a complex disorder where multifactorial interventions have been proven to improve disease control and health outcomes. Several major randomised controlled trials (RCTs) have shown reduction of complications with more intensive pharmacotherapy for hypertension, dyslipidaemia and hyperglycaemia in type 2 diabetes (T2D)[3]. A recent study compared intensive hospital-based multi-modality treatment for T2D and associated cardiovascular risk factors with usual treatment in primary care and found a 50% reduction in cardiovascular disease (CVD), nephropathy, retinopathy and neuropathy in the intensively treated group [4]. A range of self-management interventions focusing on patient education and empowerment have also been shown to be effective [5,6].

In Australia, the National Service Improvement Framework (NSIF) for Diabetes states that high quality clinical care and support are critical to improving diabetes outcomes [7]. The framework identifies the characteristics of optimal care as being based on evidence and guidelines, as well as being patient centred, structured to include goal-setting and involving PNs in delivering care. In Australia and the UK, people with T2D receive the majority of their care in General Practice. Yet GPs face barriers to providing structured multidisciplinary care for chronic illnesses such as diabetes. These barriers include the complexity and time consuming nature of chronic disease care as well as a lack of clarity about legitimate goals and outcome measures [8]. GPs' knowledge, skills, attitudes and beliefs may also significantly alter their approach to management [9,10]. In addition, people with diabetes vary in their knowledge and skills, sense of engagement, expectations of treatment, and consequent behaviour. As a result there is often a significant treatment and outcomes gap between clinical diabetes care guidelines and actual clinical practice in General Practice [11,12]. This gap is most marked in socio-economically disadvantaged communities [13-15]. The potential role for PNs to help reduce this treatment and outcomes gap through enhancing patient self-management as well as intensifying therapy, needs further study.

### Educational and psychological interventions

A meta-analysis of 31 RCTs of patient-centred education and self-management interventions in diabetes reported a mean 0.75% absolute reduction in HbA1c [5]. Ismail et al. [6] suggested educational interventions focusing on knowledge and information need to be distinguished from psychological interventions that address individuals' cognitive and emotional functioning and that the latter alone can reduce HbA1c by 1%. Many of the psychological interventions that Ismail et al. reviewed employed Rollnick & Miller's [16] motivational interviewing techniques based on the Transformational Model of Change or counseling strategies focused on Bandura's [17] theory of self-efficacy. Nevertheless, how such interventions have an effect remains unclear [18] although some experts suggest goal setting based on clinical information may be critical [19,20]

### The Coaching patients On Achieving Cardiovascular Health (COACH) intervention

The COACH program uses structured telephone coaching of patients. It is a pragmatic intervention that primes the patient to self-manage by adhering to medication and make relevant behaviour changes. It also, importantly, encourages patients to take greater initiative in the therapeutic alliance, which enables treatment to be appropriately intensified according to clinical practice guidelines in order to achieve treatment goals. The COACH model includes a structured training course for coaches and a series of scheduled and structured telephone sessions with patients addressing lifestyle issues, medication adherence and dosing, how to monitor their disease and how to consult with their GP and allied health services. The COACH intervention has been shown to effectively reduce CVD risk factors in patients with established CVD in a hospital setting using trained, dedicated coaches [21,22]. It is an appropriate model to enhance intensive diabetes treatment because many of the treatment goals are the same. However, it has not been applied or tested in a community setting, nor with PNs acting as coaches. We adapted the COACH intervention for T2D based on information derived from a series of focus groups with people with T2D undertaken to establish whether telephone coaching by PNs would be an acceptable way of managing diabetes for our target sampling population in General Practice. This qualitative phase of the study, which will be reported elsewhere, included a trial run of the PEACH study questionnaires. The PEACH study aims to test whether telephone coaching can reduce the guideline-treatment gap in people with T2D in a way that meets the characteristics of optimum care set out in the NSIF [7].

### Objectives of the study

Our primary objective is to test the effectiveness of the COACH program in improving glycaemic control at 12 and 18 months in patients with poorly controlled T2D (HbA1C >7.5%) compared with usual care only. Our secondary objective is to assess the impact of the intervention on other CVD risk factors (total cholesterol, High Density Lipoprotein (HDL) cholesterol, blood pressure, Body Mass Index (BMI)), behavioural risk factors (exercise, smoking and diet) and process of care measures (achievement of guideline based standards for monitoring, and intensification of therapy). We also plan to study the role of a range of potential explanatory variables, including socioeconomic disadvantage, in predicting outcomes.

## Methods/design

The study is a cluster-randomised, open controlled, intervention trial where General Practices in Melbourne with existing PNs are allocated to one of two groups:

• Intervention group where PNs use the COACH Program to encourage patients with T2D to undertake intensive disease self-management in combination with usual GP care.

• Control group where patients with T2D receive usual GP care only.

### Identification and recruitment of practices and patients

Figure 1 shows the recruitment process of practices and patients into the PEACH study.

**Figure 1 F1:**
[figure not shown]
Flowchart of PEACH study recruitment process.

#### Practices

GPs are approached using the membership lists of Divisions of General Practice (Divisions of General Practice are geographic organisations of GPs established in 1992 by the Government. They are local organisations that unite GPs and increase their capacity to work co-operatively with each other and other health providers[23]). The study team approached Divisions of General Practice in areas of relatively high socioeconomic disadvantage through metropolitan Melbourne and in 2 large nearby regional centres.

All GPs on the membership list of participating Divisions and who are from practices that employ PNs receive an invitation from the Division with a faxback response sheet. Interested GPs fax back to the research team their intention to participate. Non-responders are reminded by the Division staff with a telephone call one week later. The research team visits practices who express their intention to participate, explain the PEACH study in great detail and provides them with a full information pack describing the aims, methods and expected outcomes of the study, as well as consent form. Consent from all participating GPs and PNs is obtained prior to inclusion in the study. Not all GPs from the practice need to consent to participate for the practice to be included in the study. An information night is held to brief GPs and PNs about the PEACH study implementation.

#### Patients

Participating GPs obtain a list of all diabetic patients with HbA1c ordered by them and measured in the previous 12 months with a value >7.5%, from the local pathology provider. Once a list of eligible patients (see inclusion and exclusion criteria below) have been identified, a random sample of a maximum of 40 patients with HbA1c>7.5% for each practice is sent a letter inviting them to participate in the study, along with a pamphlet about the study, a plain language statement, an expression of interest form, a brief personal survey collecting demographic information and details of duration, treatment and complications of diabetes. The letter is sent using the practice letter head and is signed by the patient's GP and the pack includes a postage paid return stamped envelope addressed to the research team. A member of the research team provides support to the practice in the identification and recruitment of eligible patients. Patients respond by returning the expression of interest form to the research team. All patients, including those who decline, are asked to return the brief personal survey with their response to the letter, allowing a comparison of the participant and non-participant groups. All patients who indicate interest in participating have their details forwarded to their practice and the Practice Nurse contacts the patient to arrange a face-to-face interview at which the study is fully explained and consent is obtained. If patients consent to be included, baseline assessment is undertaken at that face-to-face interview. Patients who have not responded receive a reminder call from the Practice Nurse. If the practice has more than 40 eligible patients, further rounds of randomised mail outs and reminder calls continue until the required number of patients per practice is recruited. A further recruitment strategy of searching practice database to identify eligible patients who had their pathology tests done elsewhere is employed to minimise selection bias and reach recruitment targets of patients with diabetes.

### Inclusion and exclusion criteria

Practices with a practice nurse are eligible to participate, and must achieve a minimum recruitment of five patients to the study to continue. Patients with T2D are eligible to participate if they are >18 years, their most recent HbA1c is greater than 7.5% and they are receiving care from a General Practice that employs a Practice Nurse and is located in one of the participating Divisions of General Practice. Patients are excluded if they are not contactable by telephone, have a complex debilitating coexisting medical condition (e.g. mental illness, end-stage cancer), or do not provide signed consent. Patients from non-English speaking backgrounds are eligible and are able to utilise a free telephone interpreting service to find out more information about the study and throughout the data collection and intervention phases.

### Baseline assessment

Baseline assessment is conducted by the Practice Nurse and takes approximately one hour to complete. Patient written consent is obtained prior to undertaking baseline assessment. Baseline assessment includes data collected by the Practice Nurse at interview (patient knowledge of appropriate testing and goals for risk factors, smoking status, current exercise levels and a dietary history using a validated food frequency questionnaire [24]), from the patient file (treatment, test frequency and most recent pathology results), and patient self report data (diabetes self efficacy scale [25], the diabetes support scale[26], a quality of life scale [27] and a measure of depression [28]). Patients are instructed to arrange baseline testing for HbA1c, total and HDL cholesterol, and renal function at their usual local pathology laboratory. Follow up tests will all be done at the patients' usual pathology laboratory. All participating laboratories use HbA1c assay methods that are DCCT aligned [29] and participate in a regional quality assurance program for HbA1c assays.

### Outcome assessment

Data collected at baseline, including primary and secondary outcome measures, will be collected again at 12 and 18 months post-intervention for both the intervention and control groups. Study team nurses blinded to the group allocation of participants will collect 12 month and 18 month follow up data by face-to-face interview with the patient. We will also access administrative data sets in relation to health service use and cost.

### Randomisation

General Practices are randomised to either the intervention or control group after all baseline assessments are completed (figure 2). Block randomisation with random block sizes, stratified according to the organisational and financial arrangements of the general practices (fee-for-service private practice or state government funded community health centre status) and whether they are participating in the National Primary Care Collaboratives Program (A national pilot quality improvement program aimed at improving quality of chronic disease care and currently involving approximately 7% of general practices) is used to allocate practices to study groups. The allocation sequence is computer generated by the statistician from the research team, blinded to the identity of the general practices. Following randomisation, practices are informed by a letter from the Chief Investigator of whether their practice will be in the intervention or control group.

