### Sample size calculations

The unit of randomisation in this RCT is the general practice. A total of 546 patients (13 patients per practice) from 42 general practices will be required (273 in each arm) to show an absolute 0.5% or greater reduction in mean HbA1c in the intervention arm compared with usual GP care group. The sample size allows for a design effect of 1.4 due to the increased variance of recruiting patients within practices and an attrition rate of 20% over 18 months and overall attrition rate of 30% over 3 years in anticipation of an extension of the study for another 18 months pending funding. Calculations are based on a two sample t-test for means, with a standard deviation of 1.44 (this is based on results from a previous diabetes project in General Practice in the region involving 1,088 diabetes patients), 80% power and significance level at 5% for a two sided test. The design effect is based on a conservative estimate of the intra-cluster correlation (ICC) for HbA1c of 0.05.

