### Data collection, monitoring and analysis

Descriptive statistics will be used to summarise general practice, practice nurse and patient factors for the two study groups and to check for any imbalance in baseline variables between control and intervention group. GP practice will be set as the primary sampling unit. Outcomes between study groups will be compared to assess the effect of the intervention. Primary and secondary outcomes will be analysed using marginal models using Generalised Estimating Equations with information sandwich (robust) standard errors to allow for the effect of clustering of patients within general practices. Analysis will be 'intention to treat' and where appropriate regression analysis will be adjusted for baseline outcome measure and any baseline variables that are imbalanced between the two study groups. Sensitivity analysis will examine the effect of loss to follow-up on the intervention effect. Exploratory analyses are also planned to examine the effect of explanatory factors (e.g. socio-demographic factors such as education level or employment status of patients) on the outcome.

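### Practices are randomised within strata, but the stated covariate rule does not carry the stratification factors into the model, so the reported standard error may be somewhat too large

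*Protocol article*

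**What the plan says.** The Randomisation section of the protocol article describes "Block randomisation with random block sizes, stratified according to the organisational and financial arrangements of the general practices" (private fee-for-service practice or state-funded community health centre). It adds a second stratifier, participation in the National Primary Care Collaboratives Program, which it says involves roughly 7% of general practices.

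The section on data collection, monitoring and analysis plans marginal models by generalised estimating equations (GEE), with robust standard errors for clustering by practice. Where suitable, the regression is to be "adjusted for baseline outcome measure and any baseline variables that are imbalanced between the two study groups". Neither stratification factor is named there, and neither is ruled out.

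**The concern.** An analysis should normally reflect the restrictions placed on the randomisation. Stratified blocking removes stratum differences from the comparison between arms. A model without the strata still counts those differences as between-practice error, so its standard error does not show the gain.

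The article is not merely silent on covariates. It gives a selection rule, and the rule fits the design poorly. Selection by observed imbalance tends to pass over factors that the allocation was built to balance. Where a small stratum ends on an incomplete block, the same rule may let a factor in. Whether a design factor enters the model then depends on the data. At stake are intervals somewhat wider than they need be, a few points of power, and a primary model that is not fully fixed before the data are seen.

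**Working it through.** **Inputs from the article (Sample size calculations).** "Calculations are based on a two sample t-test for means, with a standard deviation of 1.44"; "80% power and significance level at 5% for a two sided test"; difference 0.5; design effect 1.4; ICC 0.05; 42 practices of 13, so 21 per arm; attrition 20% at 18 months and 30% at 3 years.

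**Assumed input.** f is the share of between-practice variance in follow-up HbA1c, beyond baseline, that the two factors explain. The article gives no figure. I use 0 to 0.5.

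**Step 1: reproduce the plan's figure.**
- n per arm = 2 × (1.960 + 0.842)² × 1.44² / 0.5² = 131 after rounding up (132 by the exact t-test).
- 131 × 1.4 / (1 − 0.30) = 262 (264 from 132).
- 262 / 13 = 20.2, so 21 practices per arm; 21 × 13 = 273 per arm, 546 in all. This agrees with the article.
- The design effect fits the cluster size after 30% attrition: 13 × 0.7 = 9.1, and 1 + (9.1 − 1) × 0.05 = 1.405.

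No step takes credit for stratification.

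**Step 2: standard error with and without the strata.**
- Between-practice variance = 0.05 × 1.44² = 0.1037; within-practice variance = 0.95 × 1.44² = 1.9699.
- SE without strata = √[2 × (0.1037 + 1.9699/m) / 21].
- SE with strata = √[2 × (0.1037 × (1 − f) + 1.9699/m) / 21].
- Completers per practice: m = 9.1 at 30% attrition, 10.4 at 20%.
- SE without strata: 0.1746 (m = 9.1) or 0.1671 (m = 10.4).

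Because allocation is stratified, the true spread of the estimate follows the second formula whichever model is fitted. With z = 1.96:
- type I error of the model without strata = 2 × [1 − Φ(1.96 × SE without / SE with)];
- its power = Φ[(0.5 − 1.96 × SE without) / SE with];
- power with strata = Φ(0.5 / SE with − 1.96).

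| f | SE with strata, m = 9.1 | SE overstated, m = 9.1 | SE overstated, m = 10.4 | Type I error without strata, m = 9.1 | Power without / with strata, m = 9.1 |
|---|---|---|---|---|---|
| 0 | 0.1746 | 0% | 0% | 0.050 | 0.817 / 0.817 |
| 0.1 | 0.1718 | 1.7% | 1.8% | 0.046 | 0.821 / 0.829 |
| 0.3 | 0.1659 | 5.2% | 5.8% | 0.039 | 0.829 / 0.854 |
| 0.5 | 0.1599 | 9.2% | 10.2% | 0.032 | 0.838 / 0.879 |

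The power cost at m = 9.1 is 0.8, 2.5 and 4.1 points for f = 0.1, 0.3 and 0.5.

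**Step 3: simulation.** Stratified blocked allocation of 42 equal-sized practices was simulated with uncorrected sandwich standard errors, 6,000 runs per scenario. Block sizes (2 and 4) and stratum sizes (smaller strata of 3 and 4, 6 and 6, or 14 and 14 practices) were assumed.
- Spread of the estimate at f = 0.2, smaller strata of 6 and 6: 0.1687 without stratum terms, 0.1686 with them. The estimate is equally precise either way.
- At f = 0 without terms, the sandwich SE was about 2 to 5% too small (ratio to true spread 0.955 to 0.976). This is a small-sample effect of 42 clusters and works against the overstatement in step 2.
- With terms, the sandwich SE was about 4 to 7% too small (ratio 0.927 to 0.958), and type I error was about 6.5 to 7.6%. Without terms, type I error was 5.9 to 7.0% at f = 0, 5.2 to 5.6% at f = 0.2 and 4.1 to 4.9% at f = 0.5.

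**The case against.** The strongest reply is that a journal article condenses the plan, and an exact covariate list usually belongs in a statistical analysis plan, which is not shown. The adjustment sentence is hedged and is not said to be exhaustive. This stands in part: nobody can say that the trial will leave the factors out. But the article states a rule, and the rule as stated points away from them.

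A second reply is that the harm is conditional and small. It requires the strata to predict HbA1c beyond baseline HbA1c, and no figure supports that. The ICC used here is the article's own, which it calls conservative, and no allowance is made for baseline adjustment. If the 7% share applies to this trial, about 0.07 × 42 = 2.9 practices are in the Collaboratives, so that factor can explain little. All of this stands. One counterweight is that the secondary outcomes include process-of-care measures, to which a quality improvement program is plausibly related; the article gives no figure for that either.

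A third reply is that balance is not guaranteed. About three practices cannot split evenly, and practice sizes may vary, since the eligibility section sets a minimum of five patients. The imbalance rule might then admit a factor. That is true, but it shows that inclusion would depend on the data, which is part of the difficulty.

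**Conclusion.** The point holds in a limited form. The covariate rule does not match the stratified allocation, and any effect is on the reported standard error. That is overstated by about 2% at an assumed f of 0.1, 5 to 6% at 0.3, 9 to 10% at 0.5, and not at all at 0, with a power cost of roughly 1 to 4 points. These figures assume equal practice sizes, ICC 0.05, SD 1.44 and a standard error otherwise correct for 42 clusters.

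A reader might infer more than the article supports:
- That the benefit of stratifying is lost. It is not; the allocation itself delivers the precision, and the simulated spreads are nearly identical.
- That the sample size or power is undermined. The 546 reproduces without credit for stratification, and in step 2 power without the strata stays above 80%.
- That false positives become more likely. Omitting the strata pushes type I error down. Excess in the simulation comes from the uncorrected sandwich variance, a separate matter that bears on the remedy.

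**What to change.** In the analysis section, state that practice funding type and Collaboratives participation enter the primary and secondary GEE models as fixed effects whatever the observed balance. For these two factors this replaces selection by imbalance. In the same sentence, specify a small-sample correction for the sandwich variance, with degrees of freedom based on 42 practices less the practice-level terms (42 − 4 = 38, counting intercept, arm and the two factors, against 40 without them). The two changes belong together, because stratum terms with an uncorrected sandwich error could make the test anti-conservative.

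The cost is a short addition to the text and about two practice-level degrees of freedom. No change to the sample size is needed. The gain from the Collaboratives factor may be slight if only about 3 of the 42 practices take part.
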